# Maintenance Therapy with Aromatase Inhibitor in epithelial Ovarian Cancer (MATAO): study protocol of a randomized double-blinded placebo-controlled multi-center phase III Trial

**DOI:** 10.1186/s12885-022-09555-8

**Published:** 2022-05-06

**Keywords:** Aromatase Inhibitor, Letrozole, Generic, Hormone therapy, Ovarian Cancer, Maintenance therapy, Quality of life, Randomized controlled phase III trial

## Abstract

**Background:**

A high percentage of epithelial ovarian cancers (EOC) express the estrogen receptor (ER), which is an ideal target for endocrine therapy. Letrozole is a proven, potent aromatase inhibitor, extensively tested and used in the treatment of ER positive breast cancer. In addition, it seems a potent drug for patients with heavily pre-treated OC as demonstrated in several distinctive settings. However, it has never been evaluated prospectively in a maintenance setting for ovarian cancer after standard of care. The here proposed trial aims to define a population of EOC patients, who would benefit from the effectiveness of the generic agent letrozole, with little expected toxicity and thus beneficial impact on overall quality of life (QoL).

**Methods:**

In this international multicenter randomized, placebo-controlled phase III trial at clinical centers in Switzerland, Germany and Austria, we plan to include 540 patients with primary, newly diagnosed FIGO Stage II to IV and histologically confirmed low- or high-grade serous or endometrioid epithelial ovarian/fallopian tube/peritoneal cancer. Patients are randomized in a 1:1 ratio into two groups: receiving blinded study treatment (letrozole or placebo tablets). When assuming a HR of 0.7, a median PFS of 18 months in the control arm and a median PFS of 25.7 months in the treatment arm, a two-sided alpha level of 5%, 3.5 years recruitment and 1.5 years observation time, we expect 330 events to have occurred within these 5 years in the total cohort yielding a power of 90%. Follow-up data for the whole cohort will be collected for up to 10 years and for the low-grade cancer for up to 12 years.

**Discussion:**

The here proposed randomized phase III trial aims to identify patients with EOC in the maintenance setting, who benefit from the effectiveness of the letrozole, by proving its efficacy whilst maintaining a high standard of QoL due to the limited toxicity expected in comparison to the current alternative drugs on the market for this treatment phase.

**Trial registration:**

This trial is registered at clinicaltrials.gov under the identifier NCT04111978. Registered 02 October 2019.

**Supplementary Information:**

The online version contains supplementary material available at 10.1186/s12885-022-09555-8.

## Background

The prognosis of patients with ovarian cancer is still poor with a 5-year relapse rate of 75% for advanced high grade serous and endometrioid ovarian cancers (HGOC) [1–3]. However, better treatment options including maximal cytoreductive surgical efforts and new targeted-therapies has improved the outcome of particularly HGOC over the last decade. Several drugs have been evaluated in clinical trials in the primary and recurrent setting. The most promising medical strategies to delay progression of ovarian cancer after primary surgical and adjuvant treatment as of today are (a) PARP-inhibition with olaparib [4, 5], niraparib [1], rucaparib [6, 7] and others or (b) inhibition of angiogenesis with targeting agents like bevacizumab [8–10], pazopanib [11], cediranib [12, 13], trebananib [14] and others. Bevacizumab, a vascular endothelial growth factor (VEGF)-antibody is approved for maintenance treatment based on a post-hoc analysis for high-risk cancers [15]. Olaparib, a PARP-inhibitor, is approved for high-grade serous ovarian cancer in the recurrent setting after re-introduction of platinum-based chemotherapy [15]. Additionally, Olaparib showed tremendous benefit in BRCA mutated patients in the first adjuvant SOLO-1 maintenance trial [4]

Recently, the results of three separately conducted clinical trials with various PARP inhibitors and different combination treatments, PRIMA, PAOLA, and, by Coleman et al*.,* 2019, VELIA, demonstrated substantial benefit when incorporating PARPi upfront in the treatment of newly diagnosed ovarian cancer, leading to a meaningful increase of progression-free survival [1, 5, 16]. However, with a substantial treatment discontinuation (12%-54%), dose reduction (28%-70.9%), and dose interruption (20%-79.5) due to adverse events [1, 4, 5], and with a note that, the impact of improved surgical resection techniques could not be ignored as residual disease, after upfront surgery, is still the best prognostic indicator for relapse [3].

Despite all these new treatment options and the subsequent increase on progression-free survival (PFS) for distinct groups of ovarian cancer patients, the overall survival (OS) remains poor with a high relapse rate [1, 2, 4]. This underlines the need for the exploration of treatment options that will increase PFS and OS without decreasing quality of life (QoL).

### Rationale

Anti-hormonal therapy is an old, but important treatment option with recent new and promising results on the maintenance phase of patients treated for ovarian cancer until Time to First Subsequent Treatment (TFST) [17, 18]. For early and advanced estrogen receptor (ER) positive breast cancer, endocrine therapy including maintenance phase therapy is the gold standard [19–21]. The most active drugs are tamoxifen, aromatase inhibitors and fulvestrant, which have considerably improved the prognosis for women with breast cancer [22].

Aromatase inhibitors (AIs) inhibit the estrogen production in postmenopausal women by more than 90%. In the adjuvant setting of breast cancer patients, the therapeutic effect of AIs has shown to be superior to that of tamoxifen [23].

Expression of aromatase mRNA and protein have been found in 33–81% of ovarian cancers [19]. Preclinical data has shown that the growth of ovarian cancer cells is prohibited *in vivo* and *in vitro* by the endocrine therapy against ER positive OVCAR-3 HGOC cells [22]. In addition, *in vitro* studies show an anti-tumor effect of AI on ovarian cancer cells, which was associated with aromatase activity and ER expression [24].

Several small series suggested a benefit in low-grade serous ovarian cancer (LGOC) patients, suggesting that there are subgroups of patients with a specific tumor biology that respond very well to endocrine therapy [25, 26]. LGOC is a rare histological subtype and biologically distinct from HGOC. Only approximately 5–10% of all ovarian cancers are of low-grade serous type. Gershenson et al*.* [17, 18]*,* presented retrospective analyses of endocrine maintenance therapy (with diverse regimens, including anastrozole, letrozole and tamoxifen) for LGOC. For patients receiving endocrine maintenance therapy (*n* = 70) after platinum-based adjuvant chemotherapy, PFS significantly improved as compared to patients under observation only (*n* = 133, 64.9 months; 95% CI 43.5 to 86.3; versus 26.4 months; 95% CI 21.8 to 31.0, *p* < 0.001) [17]. Most patients received treatment with letrozole (54%) or tamoxifen (28%) [13]. In 2012, the same authors described already a high clinical benefit rate in a retrospective analysis obtained from medical records ranging from 1989 until 2009 covering 64 patients with recurrent LGOC [18]. In spite of the known limitation of retrospective analyzed data as a long study period, incomplete data, potential referral bias, heterogeneous therapies, and varying follow-up practice patterns, patients receiving different regimens of endocrine maintenance therapy for relapse showed a response rate of 9% and stable disease of 62% [18]. This is of major significance as—similar to ER-positive breast cancer patients – LGOC affects mostly younger women with a rather poor prognosis [17].

The rationale for exploring endocrine therapy for the treatment of ovarian cancer patients is based on the high ER/PR expression as a predictive marker, since ovarian cancer is partly driven by the estrogen-pathway [27].

In spite of these clear distinctions between HGOC and LGOC, primary treatment strategies in both diseases have so far been similar, i.e. maximal surgical cytoreduction, followed by adjuvant chemotherapy with carboplatin and paclitaxel. None of the studies and analyses on endocrine treatment of ovarian cancer so far were prospective, in the maintenance setting, and potentially in combination with other maintenance treatments, but rather as a stand-alone treatment regimen in heavily pre-treated patients. Of note, generally no information in regards to ER/PR expression was provided.

As a pilot, we performed a small single-site prospective observation trial in 50 HGOC FIGO III/IV patients and analyzed the results together with three other patient cohorts. We found a marked improved PFS at 24 months: 60% when taking Letrozole versus 38.5% in the control group (*p* = 0.035). This effect was even more present in patients treated additionally with Bevacizumab; 20.8% of patients had no recurrence after 12 months compared to 87.5% when taking Letrozole in addition to Bevacizumab (*p* = 0.026). This positive effect was particularly evident when the treatment was initiated within three months after the end of adjuvant chemotherapy [28].

It is remarkable that endocrine treatment has only been used in the relapsed setting of ovarian cancer and that its role in primary or maintenance treatment has not been studied. Although, for more than 40 years, tamoxifen and later aromatase inhibitors have been studied in smaller cohorts and studies. A literature review covering over 50 trials including retrospective analysis, demonstrated a clinical benefit rate ranging from 0–95% when focusing on the most commonly used drugs, tamoxifen and aromatase inhibitors. These ambiguous results are probably caused by the heterogeneous patient’s characteristics and the fact that these patients received the treatment, mostly, during later lines [29].

In the relapsed setting there are little data comparing chemotherapy versus tamoxifen. One larger phase III trial in the platinum-resistant setting compares tamoxifen 40 mg/d with standard of care paclitaxel or liposomal doxorubicin. Patients on chemotherapy had longer PFS (12.7 vs. 8.3 weeks, HR, 1.54; 95% CI, 1.16–2.05; log-rank *p* = 0.003) but experienced more toxicity and poorer QoL [30]. As a result of these studies, endocrine therapy has currently been listed in the NCCN guidelines as an optional treatment strategy in the relapsed setting [31].

To our knowledge (on 14. December 2021 we searched clinicaltrials.gov and trialsearch for ongoing maintenance trials with Letrozole, using the search terms ‘ovarian cancer’, ‘ER’, ‘endocrine therapy’ and ‘letrozole’, identifying one other trial (NCT04095364) for ovarian cancer patients), there is only one other clinical trial evaluating aromatase inhibitors as a first line monotherapy and in the maintenance setting of LGOC (NCT04095364) whereas it has been commonly evaluated in the relapsed setting [29]. Furthermore, there are no QoL data of aromatase inhibitor after 1^st^ line treatment in the maintenance setting. To this end, the MATAO trial evaluates letrozole versus placebo in the maintenance setting in low and high grade serous and endometrioid ovarian cancer patients accompanied by assessment of the quality of life questionnaires EQ-5D-5L, FACT-ES, and FACT-O in combination with the CD-RISC-10 resilience, G8 fragility and ACCI comorbidity scores.

### Aims

There is a need to evaluate endocrine therapy in a prospective large phase III trial including and focusing on QoL aspects. We present a phase III randomized double-blind placebo-controlled multi-center trial that will assess the effect of the aromatase inhibitor letrozole as maintenance therapy in patients with FIGO Stage II-IV low and high-grade ovarian cancer of endometrioid or serous histotype. This experimental arm will be compared to the current standard, namely use of no maintenance endocrine therapy after the end of adjuvant chemotherapy, whereas, combined treatment with the new approved treatment options in this phase is allowed and has been proven safe [32, 33].

Based on the evidence presented above, we hypothesize that the letrozole maintenance arm will lead to a prolongation of PFS in these patients with no decrease of QoL. PFS has been selected based on previous data from our own study [28] and a recent meta-analysis [34] demonstrating a high potential benefit in regards to prolongation of the time to first relapse by 8 months using endocrine treatment in the maintenance setting.

Moreover, this study aims to identify the population that would benefit the most from this endocrine therapy in respect to prolonged quality of life (QoL). QoL will be assessed, prior, during, and after the intervention period, by both validated QoL questionnaires as well as by activity measurements. In addition, the survival status will be evaluated in relation to fragility and vulnerability as well. To this end, the G8 score will be used to assess fragility by patients over 75 years of age and the CD-RISC-10 score to assess resilience in the whole cohort.

## Methods/design

### Study design and sites

This study is designed as a parallel group, multi-center, superiority, randomized, placebo-controlled, phase III Trial within the ENGOT research network including 21 Swiss, 30 German and 8 Austrian Gynecological Cancer Centers (Fig. 1).

**Fig. 1 Fig1:**
[figure not shown]
Schematic representation of MATAO study design, covering the maximum time schedule per patient depending on the differences in in histopathological grading. *ER*   Estrogen Receptor*, **PARPi*   Poly(ADP-Ribose)-Polymerase 1 inhibitor

### Patient recruitment and screening

Potential participants are being identified during tumor board by their treating oncologist. Patients already undergoing chemotherapy are also potential study candidates, if use of the scores are routinely in place.

If the ER expression is positive and the pathology review confirmatory for both low or high-grade serous or endometrioid ovarian cancer, including fallopian tube and primary peritoneal cancer, patients undergo a second screening process after subsequent treatment with chemotherapy to ensure that the tumor has not progressed under chemotherapy. Written informed consent is obtained from each patient prior to randomization.

### Inclusion criteria

Patients must be ≥ 18 years of ageWilling and able to attend the visits and to understand all study-related proceduresPrimary, newly diagnosed FIGO Stage II to IV and histologically confirmed low or high grade serous or endometrioid epithelial ovarian/fallopian tube/peritoneal cancer(Interval-) debulking performedEastern Cooperative Oncology Group (ECOG)-Performance Status 0–2Signed informed consents (ICF-1; ICF-2)Paraffin-embedded tissue or paraffin-embedded cell block (from ascites) availablePositivity (≥ 1%) for ER expression (as determined by the central Histopathology Core Facility of the MATAO trial)At least 4 cycles of platinum-based chemotherapy (neoadjuvant allowed)Negative serum pregnancy test in women of childbearing potential (women of childbearing potential defined as: premenopausal or less than 12 months of postmenopausal amenorrhea, and who have not undergone surgical or radiation sterilization)

Note: Patients under concurrent maintenance treatment with Bevacizumab and/or PARP Inhibitors are eligible

### Exclusion criteria

Progressive disease at the end of adjuvant treatmentAny other malignancy within the last 5 years which has impact on the prognosis of the patientLess than 4 cycles of chemotherapy in totalContraindications to endocrine therapyInability or unwillingness to swallow tabletsWomen of childbearing potential (not having had nor will getting a surgical resection, prior to the intervention in the therapeutically maintenance setting)Pregnant or lactating womenPatients with a known intolerance to galactose, lactase deficiency and glucose-galactose mal-absorption

### Randomization

After written informed consent has been obtained and all eligibility information has been entered into the system and all eligibility criteria are met, the secuTrial® database will provide the study site with a unique, anonymous patient identifier (randomization number). Subjects will be assigned 1:1 to letrozole or placebo. Randomization is performed from the secuTrial® system by stratifying the grade of cell differentiation (low or high) using the variance minimization procedure. After full completion of a subject’s enrollment the secuTrial® system creates automatically a confirmation of the successful randomization process, sent via Email blinded to the individual site and the coordinating office, and unblinded to the Clinical Manufacturing Organization (CMO). 

### Blinding procedures

Physicians, study nurses, patients, outcome assessors, involved pharmacists and statisticians will be blinded to the allocated treatment. Letrozole and the placebo will be visually indistinguishable and will be provided in the same packed manner by the CMO. Neither the investigator/study team nor the patient will know what they are receiving, and it shall remain so until primary statistical analysis was performed. The CMO, who is not directly involved in the study, will label, pack and dispense the medication according to the results of the randomization procedure. Both, trial treatment and placebo are indistinguishable, apart from medication ID on the package, of which only the distributor and a dedicated person of the CRO have information.

This level of blinding is maintained throughout the trial until the primary analysis of the whole cohort. The final PFS analysis of the whole cohort in the study design of MATAO is scheduled, minimum 1.5 years after inclusion of the last patient, this will take place maximum after 5 years and 3 months. However, recruitment of LGOC patients need to be extended for another 2 years to meet the required statistical number of patients. This yields an interim analysis of the low-grade sub-group. The clinical project coordinating management, the patients and the site’s PI remain blinded for the low-grade group for the whole conduct of the trial.

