#### Sample size considerations specific for the low grade cohort, LOGOS

Assumptions about efficacy for the power calculations are based on the retrospective analysis of Gershenson et al*.* [17]. We assume exponential PFS distributions, the analysis by a two-sided log-rank test with alpha level 0.05, and a power of 80%. With an accrual duration of 7 years and a follow-up phase of 5 years after accrual of the last patient, a dropout rate of 15%, and a median PFS of 36 months in the control arm and 60 months in the experimental arm (i.e. a hazard ratio of 0.6 between arms). Because the main protocol of the MATAO trial schedules its final PFS analysis at approximately 5 years after inclusion of the last MATAO patient (while recruitment into the LOGOS stratum will still be ongoing) and states grade as a factor for subgrouping, technically, this constitutes an interim analysis of the LOGOS data. To account for this interim analysis, we plan an O’Brien-Fleming group sequential design with one interim look and one final look. The sample size / power calculations were performed using ADDPLAN version 6.1. Accounting for 15% dropout, 186 patients (i.e. approximately 2.2 patients per month) should be recruited into LOGOS in order to have the 158 evaluable patients, necessary to achieve a power of 80% with this O’Brien-Fleming group sequential design. The boundaries for the group sequential design at the interim look will be based on the actual number of observed events and will be calculated using the alpha-spending function for an O’Brien-Fleming design. The final analysis will be performed after observation of 121 events.

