### Interim analysis

No interim analysis is planned for the primary analysis on the full set of patients (HGOC + LGOC). However, since the LGOC study recruitment continues after closure of the study for the whole cohort, the subgroup analysis of the LGOC should be regarded as an interim analysis by an O`Brien-Fleming group sequential design for this cohort. The boundaries for the group sequential design at the interim look will be based on the actual number of observed events and will be calculated using the alpha-spending function for an O’Brien-Fleming design. The final analysis will be performed after observation of 121 events.

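### After the whole-cohort analysis, nothing in the text keeps outcome assessors and site staff other than the PI blinded for low-grade patients, although about two thirds of the LOGOS events would still be to come

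*Protocol article*

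**What the plan says.** Three statements in the protocol article, Blinding procedures, matter here.

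- Who is blinded: "Physicians, study nurses, patients, outcome assessors, involved pharmacists and statisticians will be blinded to the allocated treatment".
- Until when: "This level of blinding is maintained throughout the trial until the primary analysis of the whole cohort". An earlier sentence of the section sets the same end point for the study team and the patient.
- What continues for low-grade patients: the sentence covers coordinating management and patients, and says of each site that its "PI remain blinded for the low-grade group for the whole conduct of the trial".

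The same section times the whole-cohort PFS analysis at "minimum 1.5 years after inclusion of the last patient, this will take place maximum after 5 years and 3 months", and extends low-grade recruitment by another two years. The LOGOS sample size section gives another timing: the main protocol "schedules its final PFS analysis at approximately 5 years after inclusion of the last MATAO patient". It adds that this falls "while recruitment into the LOGOS stratum will still be ongoing". For LOGOS, the Interim analysis section states: "The final analysis will be performed after observation of 121 events".

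**The concern.** The list that continues is shorter than the list that ends. Outcome assessors, study nurses, physicians other than the PI, pharmacists and statisticians are on the first and not on the second. The article does address blinding of this stratum after the whole-cohort analysis, so the gap lies in a stated rule and is not simply a topic left to another document.

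LOGOS is more than a descriptive subgroup. It has a two-sided 5% log-rank test, 80% power and a group sequential boundary. Its endpoint is PFS, which depends on assessment. Study nurses hand out the tablets at consultations (Intervention section). If assessors or site staff knew the allocation, progression calls in the later part of LOGOS could be affected, in a comparison presented as double-blind. Once allocation is known, blinding cannot be restored.

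**Working it through.** **Side by side**

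| Group | Blinded up to the whole-cohort analysis | Named as blinded afterwards (low-grade) |
|---|---|---|
| Patients | yes | yes |
| Site PI | yes (as physician) | yes |
| Coordinating management | not listed by name | yes |
| Other physicians | yes | no |
| Study nurses | yes | no |
| Outcome assessors | yes | no |
| Pharmacists | yes | no |
| Statisticians | yes | no |

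**Inputs** (LOGOS sample size section unless noted): accrual 7 years = 84 months; follow-up 5 years; median PFS 36 and 60 months; HR 0.6; two-sided alpha 0.05; power 80%; 186 recruited for 158 evaluable; 121 final events; 1:1 allocation (Randomization). The whole-cohort analysis falls at 5 years (3.5 + 1.5, Abstract) to 5 years 3 months (Blinding procedures).

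**The plan's own figures**
- Events (Schoenfeld): 4 × (1.960 + 0.842)² / (ln 0.6)² = 31.40 / 0.2609 = 120.3, rounded up to 121. Reproduced.
- Patients: 158 / 0.85 = 185.9, rounded up to 186; 186 / 84 = 2.2 per month. Reproduced.
- Consistency: the exponential model below gives 120.4 events from 158 patients at 12 years, in line with 121.

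**LOGOS events by the whole-cohort analysis.** With uniform accrual over A = 84 months and exponential PFS, the expected number of events at time T (T below A) is

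E(T) = N / (2A) × Σ over arms of [T − (1 − e^(−λT)) / λ], with λ = ln 2 / median.

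λ is 0.01925 per month (control) and 0.01155 (letrozole), and N = 158.

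- T = 60: control 60 − 0.6850/0.01925 = 24.4; letrozole 60 − 0.5000/0.01155 = 16.7. E = 158/168 × 41.1 = 38.7. Still to come: 121 − 38.7 = 82.3 (68%).
- T = 63: control 26.5, letrozole 18.2. E = 158/168 × 44.7 = 42.1. Still to come: 78.9 (65%).

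**Patients still to be enrolled** at 60 months: 186 × 24/84 = 53 (29%).

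**Sensitivity of the share still to come**

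| Assumption | Share of 121 events |
|---|---|
| 158 evaluable, 5 to 5.25 years | 68% to 65% |
| All 186 patients, no dropout, 5 to 5.25 years | 62% to 59% |
| Range over all dropout treatments tried, 5 to 5.25 years | 59–69% |
| Low-grade accrual completed in 5.5 years (3.5 + 2) | 48–59% |
| LOGOS section timing read literally (3.5 + 5 = 8.5 years) | 13–31% |

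The last row conflicts with the ceiling of 5 years 3 months in Blinding procedures. It also conflicts with the LOGOS section's own remark that recruitment is still running then, because 8.5 years lies beyond the 7-year accrual.

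**The case against.** The strongest reply is that the text never says anyone will be unblinded. The sentence on low-grade patients is an assurance without the word *only*, and its three parties could be shorthand for the trial team, the sites and the participants. Other safeguards are not said to lapse: the tablets look alike, only the distributor and one dedicated CRO person hold the medication ID information, and the randomization email is blinded to the site and the coordinating office. A site could hardly tell its nurses the allocation and keep it from its PI. Patients and PIs, who bear most on retention, are covered, and the final LOGOS analysis has a fixed event trigger. The article is condensed, and role-by-role unblinding rules may stand in the full protocol.

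Much of this stands. A reader might infer that assessors and site staff will be unblinded at year 5; the document does not support that. It ends their protection and does not renew it.

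A reader might also infer that every trial statistician should stay blinded for low-grade patients. That does not follow. The primary analysis includes these patients, stratified by grade; it is repeated within grade; and LOGOS has an interim look. Whoever runs these analyses needs low-grade data by arm.

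Nor can a type I error for LOGOS be derived. The document gives no basis for how far known allocation would shift progression calls.

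What the reply does not remove is that an explicit end date applies to six groups and the explicit continuation leaves out the outcome assessors.

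**Conclusion.** The point holds as a gap in a stated rule; it is not a demonstrated loss of blinding. Followed as written, the section stops protecting outcome assessors, other site physicians, study nurses and pharmacists at the whole-cohort analysis, while LOGOS is still recruiting and about 79 to 82 of its 121 PFS events (65–68%) are still to be assessed. That size rests on the timing in Blinding procedures, uniform accrual over 7 years, exponential PFS with medians of 36 and 60 months, and 158 evaluable patients. Under the later timing in the LOGOS section the share is smaller. The gap in wording is the same on every reading. No size can be put on any resulting bias.

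**What to change.** Amend the last sentence of Blinding procedures. Outcome assessors, all site physicians, study nurses and pharmacists, together with patients, site PIs and coordinating management, should remain blinded to low-grade allocation until the final LOGOS analysis. Low-grade allocation and by-arm low-grade results should be restricted to the statisticians who run the whole-cohort and interim analyses and to any monitoring board.

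Reconcile the timing of the whole-cohort PFS analysis between Blinding procedures and the LOGOS sample size section, so that it is clear how long the extended blinding must last.

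The cost is one sentence on blinding and one on timing. No patients, visits, events or procedures are added, and no design figure changes. The practical consequence is that the low-grade part of the by-grade subgroup analysis is withheld from sites and coordinating management until LOGOS is final. The amendment must be in place before the whole-cohort analysis.
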